## Objective

Despite the numerous studies on the myocardial protective effects of different drugs and measures, there are only a handful of drugs and measures that can be safely and effectively applied to clinical practice [1, 20]. Our research is a large sample RCT conducted to assess whether intralipid postconditioning undergoing cardiopulmonary bypass surgery will reduce the all-cause mortality within 30 days after surgery and the rate of serious complications during hospitalization and improve the patient’s postoperative cardiac function. The outcome is expected to be the foundation for the future multicenter clinical trial to evaluate the potentially clinically relevant benefit of intralipid therapy. As has been safely and widely used in clinical practice, intralipid may play a novel and important role as a therapeutic intervention for ischemic heart diseases, if similar cardioprotective effects and better clinical outcomes are demonstrated clinically.

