### Study endpoints

The primary endpoints are complex morbidity of major complications during hospitalization (all systemic organ complications are graded as I–V in Table 1) and all-cause mortality within 30 days after surgery. Each individual outcome of the composite endpoint will be analyzed separately.

**Table 1 Tab1:** Grade of complication outcome of the subjects

Grade of complication outcome of the subjects	
I	Healed after temporary treatment
II	Lead to longer hospital stay
III	Life-threatening, but can be basically recovered during hospitalization
IV	Resulting in injuries for 30 days or longer after surgery, the quality of life is significantly reduced
V	Death within 30 days after the surgery (during the study period)

Note: The end of the operation until 24:00 on the day is 0 days after surgery, and the next day after surgery is 00:01–24:00 and so on

The secondary endpoints include (1) all-cause mortality 6 months and 1 year postoperatively; (2) the quality of life within 1 year after surgery, using the 15-item Quality of Recovery Questionnaire (QoR-15) [21, 22]; (3) the postoperative cardiac function evaluated by LVEF, LVEDS, and LVEDD at time points of 1 week, 1 month, 6 months, and 1 year postoperatively, and the myocardial injury evaluated by CK-MB, cTnT, and BNP at time points of 2 h and 24 h postoperatively; and (4) short-term clinical outcomes during hospitalization (postoperative awakening time, mechanical ventilation time, ICU time, length of hospital stay) and total cost are also detailed evaluated.

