### Data collection

All the related data are collected on the CRF. Preoperative data include general information about age, height, weight, and current and past medical history, especially heart disease history. The classification of the American Society of Anesthesiologists (ASA) was used to assess the risk within 24 h before surgery. Intraoperative data include the type and duration of surgery procedure, duration of CPB and aortic cross-clamp, method of anesthesia, and duration of anesthesia. Postoperative data include the morbidity and mortality; cardiac function evaluated by LVEF, LVEDS, and LVEDD; myocardial injury evaluated by CK-MB, cTnT, and BNP; short-term clinical outcomes during hospital stay (postoperative awakening time, mechanical ventilation time, ICU time, length of hospital stay); and total cost. The follow-up data include quality of life at three time points (1 month, 6 months, and 1 year), using the 15-item Quality of Recovery Questionnaire (QoR-15) and the echocardiography to evaluate the cardiac function.

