### Data analysis

SPSS 22.0 software (IBM Co., Armonk, NY, USA) will be used to analyze the data. Baseline characteristics will be compared using chi-squared or Fisher’s exact tests. The continuous variables that have a normal distribution will be presented as the mean ± standard deviation (SD) or numbers (percentages) and compared using the *t* test or nonparametric test. The incidence of primary and secondary endpoints was measured using the chi-squared test or Fisher’s exact tests. A sensitivity analysis using the modified intention to treat (mITT) approach will also be performed. As a composite outcome, each individual outcome should be analyzed individually. Subgroup classification will be performed according to different types of surgery, Cox analysis will be used to analyze the mortality of different types of surgery, and multivariate logistic regression analysis will be used to correct for risk factors. Variables tested in the model will be selected if *P* < 0.10 or if they are clinically relevant. Results are considered statistically significant if *P* < 0.05. Two-sided significance tests will be used throughout.

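### Improved cardiac function is a stated objective, but it rests on 12 separate echo comparisons, each judged at P < 0.05, with no lead measure or time point

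*Protocol article*

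**What the plan says.** The Objective section names three things that intralipid is to be assessed on: 30-day mortality, "the rate of serious complications during hospitalization and improve the patient’s postoperative cardiac function". Cardiac function therefore stands beside the two primary outcomes in the aim, although Study endpoints classes it as secondary.

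Study endpoints defines it as "the postoperative cardiac function evaluated by LVEF, LVEDS, and LVEDD at time points of 1 week, 1 month, 6 months, and 1 year postoperatively". The other secondary endpoints are:

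- "all-cause mortality 6 months and 1 year postoperatively";
- "the myocardial injury evaluated by CK-MB, cTnT, and BNP at time points of 2 h and 24 h postoperatively";
- "postoperative awakening time, mechanical ventilation time, ICU time, length of hospital stay) and total cost are also detailed evaluated";
- the QoR-15. Study endpoints places it only within one year of surgery. The assessment times are in Postoperative follow-up and in Data collection: "quality of life at three time points (1 month, 6 months, and 1 year").

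Data analysis names a t test or nonparametric test for continuous variables and chi-squared or Fisher's exact tests for incidences. It adds Cox and logistic models for mortality by type of surgery and for risk adjustment. The threshold is then set once for everything: "Results are considered statistically significant if *P* < 0.05. Two-sided significance tests will be used throughout". The article names no lead measure, lead time, repeated-measures test, ordering or exploratory label for the secondary endpoints.

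**The concern.** An objective needs a decision rule. The article supplies one that can be met in 12 ways for cardiac function, because any of three measures at any of four visits may fall below 0.05. Followed as written, the plan could support a claim of better cardiac function from one low P value at one visit, and the chance of such a result under no effect is several times the 5% that the reader is told.

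The Objective also says that the outcome is meant to be the basis for a later multicentre trial, so a chance finding at one visit could be carried forward. A null result is realistic here. The Background reports that the pilot found no significant difference in LVEF or in the short-term clinical outcomes, which it puts down to small size. The Discussion says that no drug has proved beneficial for myocardial protection in large-scale studies.

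**Working it through.** **The plan's own figure.** The article gives no error rate for the secondary endpoints, so there is none to reproduce. Its only related figure is the sample size, which concerns the primary outcome. With 27% against 18.9% (reading the stated 30 as a 30% relative reduction), two-sided 0.05, 80% power and a continuity correction, I get 447 per group. Allowing for 10% loss, this is 447/0.9 ≈ 497 per group, or 994 in all, which agrees with about 1000. The present point does not touch it.

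**Count of comparisons**

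| Family | Comparisons | Source |
|---|---|---|
| Echo | 3 measures × 4 times = 12 | Study endpoints |
| Biomarkers | 3 × 2 times = 6 | Study endpoints |
| QoR-15 | 3 times = 3 | Postoperative follow-up; Data collection |
| Later mortality | 2 times = 2 | Study endpoints |
| Short-term outcomes and cost | 4 + 1 = 5 | Study endpoints |
| **Total** | **28** | |

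One test per measure and time is my inference from the listed methods and times. The last two families are not all measure-by-time readings, but each item is still a separate comparison.

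**Independent tests, no effect.** The chance of at least one P < 0.05 among k tests is 1 − 0.95^k. Counting only results that favour intralipid, it is 1 − 0.975^k.

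- k = 12: 1 − 0.95^12 = 46%; favourable only, 1 − 0.975^12 = 26%.
- k = 28: 1 − 0.95^28 = 76%; favourable only, 1 − 0.975^28 = 51%.

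**Correlated tests.** The article gives no correlations, so r is assumed. With a common correlation r, each test statistic is √r·u + √(1−r)·e, with u and e standard normal. The chance of any |z| > 1.96 among k tests is

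1 − ∫ φ(u) [Φ((1.96 − √r·u)/√(1−r)) − Φ((−1.96 − √r·u)/√(1−r))]^k du.

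The favourable-only version drops the second Φ term.

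| Set | Assumption | Independent | r = 0.5 | r = 0.7 |
|---|---|---|---|---|
| 12 echo, either direction | common r | 46% | 32% | 23% |
| 12 echo, favourable only | common r | 26% | 16% | 12% |
| All 28, either direction | r within families, 0 between | 76% | 65% | 55% |
| All 28, either direction | r common to all 28 | 76% | 49% | 33% |

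The third row combines the five families (12, 6, 3, 2 and 5 tests) as if independent of one another:

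- r = 0.5: 1 − (0.681 × 0.793 × 0.875 × 0.909 × 0.817) = 65%.
- r = 0.7: 1 − (0.768 × 0.836 × 0.891 × 0.917 × 0.852) = 55%.

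**Expected number of false positives among 28.** 28 × 0.05 = 1.4, whatever the correlation.

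**The case against.** The best defence has three parts.

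First, the article states a conventional threshold. It does not say that one low P value establishes better cardiac function, or that every measure is tested at every visit. A condensed article may leave the ordering of secondary endpoints to a full protocol or analysis plan that is not shown. This stands in part: separate testing is an inference, and silence alone would be no finding. But the article is not silent. It sets one threshold for all results and names only two-group tests for continuous measures, so a later plan with a lead test or a repeated-measures model would be departing from it.

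Second, cardiac function is labelled secondary, the trial is sized on complex morbidity, and the closing summary speaks only of potential evidence expected from the results. Unadjusted tests of secondary endpoints are common. That would be enough if cardiac function were exploratory, but the Objective lists it among the things the trial is conducted to assess.

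Third, the size is easily overstated. A reader might infer that the plan is likelier than not to yield a false claim of better cardiac function. The figures do not support that. The 12 echo tests stay below one half throughout, and improvement means a favourable result, for which the chance is 12% to 26%. A figure above one half in either direction needs all 28 comparisons, including cost and results pointing to harm. Even then it depends on little or no correlation between families. That is doubtful for measurements on the same patients, and with r = 0.5 common to all 28 the figure is 49%. This objection stands in full.

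**Conclusion.** The point holds for the cardiac-function objective. With no lead measure or time, and each of 12 comparisons judged at 0.05, the chance of at least one significant echo result under no effect is 23% to 46%. In the favourable direction it is 12% to 26%, about five to ten times the nominal 2.5%. These ranges run from independence to an assumed common correlation of 0.7, and they rest on separate testing of each measure and time.

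For the whole secondary set, the either-direction chance runs from 76% if independent down to 33% at a common correlation of 0.7. A statement that a spurious secondary result is more likely than not should therefore not be made without its correlation assumption. Nor does the article promise that one low P value will be taken as proof of benefit; the weakness is that its rule does nothing to prevent that reading. This is a badly fixed rule that should be changed. It does not undermine the primary analysis.

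**What to change.** In Data analysis, limit the blanket threshold and add, in substance:

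- The conclusion on cardiac function rests on one prespecified test. LVEF at 1 week, 1 month, 6 months and 1 year is analysed in one repeated-measures (mixed) model, with a single overall treatment test at two-sided 0.05.
- LVEDS, LVEDD, LVEF at single time points and the other secondary endpoints are reported as between-group differences with 95% confidence intervals. They are labelled exploratory and are not described as significant.

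LVEF is the natural lead, since it is listed first and is the echo measure that the Background reports for the pilot. What matters most is that one measure and one test are named before analysts learn the allocation. If the investigators also want confirmatory claims on other secondary endpoints, they could name a lead for each and apply Holm across them. That is optional and not needed to resolve this point.

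The cost is wording only: the data are already being collected and no patients are added. The downside is that fewer secondary results can be called significant.

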## Discussion

Despite advances in surgical technique, anesthesia management, and CPB technology, myocardial I/R injury is still an important factor affecting patients’ cardiac function and clinical prognosis. Ischemic preconditioning and/or postconditioning [24, 25] has been reported to be effective in reducing myocardial I/R injury. This method did not translate into clinical practice partially due to difficulty in the application of ischemic conditioning [25]. Remote ischemic preconditioning (RIPC) prior to cardiac surgery is non-invasive, but recent clinical studies and meta-analysis did not show its benefits on clinical outcomes [26]. Therefore, pharmacological preconditioning or postconditioning has better research and clinical prospects. Even multiple drugs were assessed [1, 20], but none proved to be beneficial in large-scale studies for myocardial protection. Now, intralipid may play a novel and potential role in cardioprotection with bright prospect [3–7].

Intralipid, a safe fat emulsion for human use, is used commonly as a component of parenteral nutrition in clinical practice. It also is used as therapy for severe cardiotoxicity secondary to accidental overdose of local anesthetics, an effect that has been confirmed in animals and humans [8–11]. Because patients with local anesthetic-induced cardiac arrest are considered to be less responsive for standard resuscitation methods, currently, infusion of lipid emulsion is considered the primary treatment for local anesthetic toxicity [10, 11]. In recent years, another striking experimental finding is that intralipid postconditioning (ILPC) could reduce myocardial I/R injuries and thus improve cardiac function, where intralipid was administered as a bolus at the onset of reperfusion [12–17]. So, intralipid may represent a novel and clinically feasible cardioprotective strategy that is highly effective in remodeled hearts. Does the protective effect of lipid emulsion play some role in the effects of propofol (where 10% lipid emulsion is the vehicle) that have been noted in myocardial I/R injury [27]? Therefore, it is necessary that the cardioprotective effects of intralipid need to be clinically verified separately.

Our research group has conducted a pilot study and showed promising results that ILPC induced a significant reduction of postoperative cTnT and CK-MB release in patients undergoing cardiac valve replacement surgery [18, 19]. Moreover, a single intravenous bolus of intralipid (2 mL/kg, 20% intralipid) did not bring abnormal lipid metabolism and was found to be safe, with no perioperative hepatic or renal dysfunction or any other significantly related complications [18, 19]. However, the sample size of the pilot study is small, and it is uncertain to know its influence on patient outcome. Here, we continue to conduct a large sample RCT to further study whether it could improve the cardiac function, the short-term and long-term clinical prognosis of adult cardiac surgery patients, not limited to valve replacement surgery. To our knowledge, this is the first clinical trial investigating the effects of intralipid postconditioning on patient outcome, including mortality, morbidity, and long-term life quality. Our data will provide a rationale for the evaluation of the potentially clinically relevant benefit of intralipid therapy.

Our research has certain limitations. First of all, due to intralipid being white emulsion, it was difficult to achieve the blinding of anesthetists and perfusionists. So even they will provide the trial intervention, but they will not be involved in either the postoperative treatment or the analysis. Secondly, since the inhaled anesthetic sevoflurane is considered to be significantly cardioprotective and the high-dose propofol has also been reported to have a certain myocardial protective effect [27–29], both of which are currently widely used in clinical anesthetics, how to reduce their interference on the results of intralipid postconditioning is of great importance. In our previous pilot study [18, 19], all included patients were given total intravenous anesthesia to eliminate the interference of sevoflurane. However, this does not rule out the role of propofol and is also not consistent with clinical practice. Therefore, in this large sample RCT, we do not limit the anesthesia methods, but will make strict statistics on the dosage of various anesthetics in the intervention group and the control group, so as to ensure the baseline data be comparable. Thus, the confounding factors and interference of the anesthetics will be effectively avoided, and at the same time, it was more consistent with the clinical routine.

In summary, this large sample RCT will be the first to explore the intralipid postconditioning on the clinical outcome of adult cardiac surgery patients. The results are expected to provide potential evidences about whether intralipid postconditioning could reduce the morbidity and mortality and improve the cardiac function and quality of life. Therefore, the results will provide a rationale for the evaluation of the potentially clinically relevant benefit of intralipid therapy.

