## Methods and design

### Study design

This iCPB study is a large sample, single-center, prospective, double-blinded, two-armed, randomized controlled trial with a 1:1 allocation ratio, testing the clinical outcome of intralipid postconditioning in adult cardiac surgery patients undergoing cardiopulmonary bypass. The protocol structure is written according to the Consolidated Standards of Reporting Trials (CONSORT) 2010 Statement guidelines and follows the Standard Protocol Items: Recommendations for Interventional Trials (SPIRIT) Statement. The SPIRIT checklist can be found in Additional file 1. The SPIRIT figure is illustrated in Fig. 1, and the flow chart in Fig. 2. The study will be conducted in West China Hospital of Sichuan University, China. More than 2500 open-heart procedures with CPB are performed there each year.

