### Randomization/blinding

Patients who meet the enrollment criteria will be randomized 1:1 to either control or ILPC group. Randomization will be performed with the use of a computer-generated randomization sequence from a random number table. The investigator who is responsible for grouping visits the patients the day before surgery and gets the informed consent. Once the patient is qualified, he determines the serial number and the random number of the patient and writes on the case report form (CRF). Any intraoperative event or deviation from the protocol is recorded on the CRF. Allocation concealment was maintained until the time of CPB initiation by using opaque, numbered, and sealed envelopes. Other researchers, such as data collectors and data analysts, will be unaware of the patient grouping. The perfusionists will be aware of patients’ group allocation because they will provide the trial intervention, but they will not be involved in either the postoperative treatment or the analysis. Due to the color difference between intralipid and saline, the intravenous infusion of the two fluids will be shielded.

The patients, surgeons, ICU physicians, data collectors, and data analysts are not aware of the trial grouping in the whole process; if patients are seriously ill, then unblinding will need to be undertaken. Any intraoperative event or deviation from the protocol is recorded on the CRF.

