### Perioperative management and monitoring

Upon arrival in the operating room, standard monitoring includes 5-lead electrocardiogram (ECG) and pulse oximeter. A peripheral venous cannula will be inserted, and patients will be sedated with midazolam intravenously. A radial arterial cannula will be inserted before anesthesia. Intravenous anesthesia is induced with midazolam (0.1–0.2 mg/kg), sufentanil (0.5–1 μg/kg), and rocuronium (0.6 mg/kg). The trachea will be intubated, and mechanical ventilation will start to achieve an end-tidal carbon dioxide tension of 35–45 mmHg, with limited inhaled oxygen concentration (FiO2) 0.4–0.6 and tidal volume (VT) 10 mL/kg during operation. After the induction, anesthesia will be maintained with continuous infusion of propofol 80–100 μg/kg/min or inhalation anesthesia 0.5–2 minimal alveolar concentration (MAC) combined with dexmedetomidine 0.5 μg/kg/h. Midazolam, sufentanil, and rocuronium will be given as needed. Arterial blood pressure, central venous pressure, and nasopharyngeal temperature will be recorded continuously. After systemic heparinization (3 mg/kg, activated clotting time > 480 s), the ascending aorta and superior and inferior lumen (or right atrium) will be cannulated. Standard CPB with a disposable hollow fiber membrane oxygenator (Affinity NT 541; Medtronic, USA) and a roller pump (Stockert-5, Sorin Group, Germany) will be started with a target output of 2.4~2.8 L/min m^2^ of body surface area. After aortic cross-clamping, cardio protection will be provided by cold-blood cardioplegia (1:4) at the dose of 20 mL/kg. The cardioplegia will be repeated half dose every 25 min during surgery. Surgery will be performed under mild hypothermia (33 °C), with MAP 50–70 mmHg and HCT 20–30% during CPB. After the cardiac surgical procedure, the heart will be defibrillated after aortic unclamping, if sinus rhythm does not resume spontaneously. After weaning from CPB, protamine will be used to reverse the effect of heparin. Patients will be transferred to ICU after surgery and extubated at the earliest clinically appropriate time when their ventilation, hemodynamics, and neurological status are considered stable by the attending physician.

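### The methods and the limitations disagree on whether anaesthetists give the infusion and may know the arm, which weakens the blinding behind awakening and ventilation times

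*Protocol article*

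**What the plan says.** The Study design section calls the trial a "large sample, single-center, prospective, double-blinded, two-armed, randomized controlled trial with a 1:1 allocation ratio".

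The Randomization/blinding section gives one unblinded role and its reason: "The perfusionists will be aware of patients’ group allocation because they will provide the trial intervention". It adds a physical measure: "Due to the color difference between intralipid and saline, the intravenous infusion of the two fluids will be shielded". It then lists the blinded parties: "The patients, surgeons, ICU physicians, data collectors, and data analysts are not aware of the trial grouping in the whole process". Anaesthetists appear neither among those aware of the arm nor among those blinded to it.

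The limitations paragraph of the Discussion names two roles: "due to intralipid being white emulsion, it was difficult to achieve the blinding of anesthetists and perfusionists". The next sentence reads: "So even they will provide the trial intervention, but they will not be involved in either the postoperative treatment or the analysis".

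Perioperative management and monitoring leaves part of the anaesthetic to discretion: "Midazolam, sufentanil, and rocuronium will be given as needed". The short-term outcomes under Study endpoints are "postoperative awakening time, mechanical ventilation time, ICU time, length of hospital stay".

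**The concern.** From the methods alone, a reader would conclude that one role, the perfusionist, knows the arm and that shielding protects the rest of the theatre team. From the limitations, a reader would conclude that the anaesthetist may know it too and may take part in giving the infusion. The protocol does not settle which is meant.

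The difference matters because the anaesthetist remains in charge of the patient after the infusion, through weaning from bypass to handover in ICU. Sedative, opioid and relaxant doses in that interval can affect how soon a patient wakes and, to a lesser degree, how long the patient stays ventilated. If the arm is known, those doses could drift apart between arms without any intent. A difference in these outcomes could then appear without an effect of the lipid emulsion and still be read as a double-blind result.

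**Working it through.** No figure in the protocol bears on this point, so the check is a comparison of sections.

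1. **Who gives the infusion.** Randomization/blinding: perfusionists. Discussion, limitations: the pronoun follows directly on anaesthetists and perfusionists, so on its natural reading it covers both. These do not match.

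2. **Who may know the arm.** Randomization/blinding: perfusionists are stated to be aware, five other parties are stated to be unaware, and anaesthetists are not mentioned. Discussion: blinding of anaesthetists is described as difficult. This is a silence in one place and a concession in another.

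3. **Whether the anaesthetist needs to know.** The methods already make the perfusionist the provider and already shield the infusion, and they rely on this to keep surgeons in the same theatre blinded. Nothing stated there requires the anaesthetist to see the fluid. The colour of the emulsion therefore does not make anaesthetist unblinding unavoidable.

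4. **What the safeguard covers.** It excludes these staff from postoperative treatment and from analysis. The infusion is given shortly before aortic unclamping (Interventions). Weaning from bypass, heparin reversal and transfer to ICU follow (Perioperative management and monitoring). Anaesthetic dosing in that interval is intraoperative, so the safeguard does not reach it.

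5. **What other protection exists.** Extubation takes place after transfer to ICU, once the attending physician judges the patient stable. ICU physicians and data collectors are both listed as blinded. The Discussion also plans to record and compare anaesthetic doses between the arms.

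6. **What follows for each outcome.** Awakening time is the most exposed, since residual intraoperative drug effect bears on it directly. Ventilation time is exposed less directly, because its end is a decision made in ICU. An effect on ICU time could follow only through these two, and the document gives no basis for sizing it.

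7. **Whether the dosing ranges measure the exposure.** They do not. The inhaled range is 2 / 0.5 = 4-fold, but the propofol range is only 100 / 80 = 1.25-fold. Both apply from induction onward, and only doses given after the infusion is seen can respond to its colour.

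**The case against.** The strongest reply is that nobody is misled. The methods never say that anaesthetists are blinded, and the authors disclose the difficulty as their first limitation, so the double-blind label is qualified within the same article. This stands in part: it is an omission followed by a concession, not a flat contradiction about blinding status. It does not settle who gives the infusion, where the two places differ.

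A second reply is that the limitation says blinding was difficult, not that it failed. That is right. A reader might infer that anaesthetists are definitely unblinded and deliver the infusion themselves. The document does not establish this: the wording on blinding is softer, and the methods assign delivery to perfusionists. The limitations sentence makes awareness likely without proving it.

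A third reply is that the outcomes remain protected by blinded ICU physicians, blinded data collectors and the planned comparison of anaesthetic doses. This stands against any claim that awakening and ventilation times are unprotected. It does not close the gap. Blinded ICU staff receive a patient whose last doses have already been given. A comparison of doses can show a difference between arms but cannot prevent one. The Discussion also treats the doses as baseline data, whereas doses given after the infusion are not baseline.

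**Conclusion.** The point holds as an inconsistency to be reconciled and a gap in the stated safeguard. It concerns two of the four short-term secondary outcomes: awakening time and, less directly, ventilation time. Their protection is weakened, not removed. The amount of bias, if any, cannot be worked out from the document. The planned total of 1000 patients says how many could be exposed, not how many are. The point gives little reason to doubt 30-day mortality.

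The conclusion rests on three assumptions:
- the pronoun in the limitations covers anaesthetists as well as perfusionists;
- the as-needed drugs during the operation are given by the anaesthetist, whom the protocol does not name for this task;
- the attending physician who decides on extubation is one of the ICU physicians listed as blinded.

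If the third is wrong, ventilation time is more exposed than stated here.

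The correction is worth making because it is cheap and removes an avoidable route of performance bias.

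**What to change.** - Reconcile the Randomization/blinding section with the limitations. State that the perfusionist alone prepares and gives the infusion in both arms.
- Extend the existing shielding to the anaesthetist: preparation out of sight, with a covered syringe and line. List anaesthetists as blinded for patients treated from then on.
- Keep the stated limitation for patients already treated, and qualify the double-blind label for them in reports. Recruitment opened in July 2019 (Trial status), so new covers cannot protect those patients, and deleting the limitation would misdescribe what was done. If recruitment has ended, only the reporting steps apply.
- Record on the CRF any case where the anaesthetist learned the arm, and report these by arm.
- Report by arm the anaesthetic doses given after the start of infusion, separately from earlier doses.
- Keep all randomised patients in the awakening- and ventilation-time comparisons. Dropping those whose anaesthetist became aware would select on an event after randomisation. If the sight of white emulsion is what reveals the arm, the exclusions would fall mainly in the ILPC arm.

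The cost is protocol wording, opaque covers and one CRF item. The perfusionist is already the stated provider, so this calls for no new role. The small downside is that the perfusionist prepares the infusion alone.
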